## Abstract

**Background:**

Kidney transplantation is the only curative treatment option for end-stage renal disease. The unavailability of adequate organs for transplantation has resulted in a substantial organ shortage. As such, kidney donor allografts that would have previously been deemed unsuitable for transplantation have become an essential organ pool of extended criteria donor allografts that are now routinely being transplanted on a global scale. However, these extended criteria donor allografts are associated with significant graft-related complications. As a result, hypothermic oxygenated machine perfusion (HOPE) has emerged as a powerful, novel technique in organ preservation, and it has recently been tested in preclinical trials in kidney transplantation. In addition, HOPE has already provided promising results in a few clinical series of liver transplantations where the liver was donated after cardiac death.

**Objective:**

The present trial is an investigator-initiated prospective pilot study on the effects of HOPE on extended criteria donor allografts donated after brain death and used in kidney transplantation.

**Methods:**

A total of 15 kidney allografts with defined inclusion/exclusion criteria will be submitted to two hours of HOPE via the renal artery before implantation, and are going to be compared to a case-matched group of 30 patients (1:2 matching) who had kidneys transplanted after conventional cold storage. Primary (posttransplant dialysis within 7 days) and secondary (postoperative complications, early graft function, duration of hospital and intensive care unit stay, and six-month graft survival) endpoints will be analyzed within a six-month follow-up period. The extent of ischemia-reperfusion injury will be assessed using kidney tissue, perfusate, and serum samples taken during the perioperative phase of kidney transplantation

**Results:**

The results of this trial are expected in the first quarter of 2020 and will be presented at national and international scientific meetings and published in international peer-reviewed medical journals. The trial was funded in the third quarter of 2017 and patient enrollment is currently ongoing.

**Conclusions:**

This prospective study is designed to explore the effects of HOPE on extended criteria donor kidney allografts donated after brain death. The present report represents the preresults phase.

**Trial Registration:**

Clinicaltrials.gov NCT03378817; https://clinicaltrials.gov/ct2/show/NCT03378817

## Introduction

Since Joseph Murray’s pioneering efforts in 1954, allogenic kidney transplantation has evolved as the standard treatment for end-stage renal disease [1]. In 2018, approximately 8000 patients were waiting for kidney transplant in Germany, but only 2005 transplant procedures using postmortem organs were performed due to organ scarcity [2]. Several strategies for donor pool expansion are being pursued concurrently. These include the use of old donors, living donors, and extended criteria donor (ECD) allografts for kidney transplant. However, ECD-allografts exhibit poor tolerance to ischemia-reperfusion injury (IRI), an important cause of kidney damage [3,4]. As such, IRI is usually the underlying cause of graft dysfunction in ECD kidney transplant [5]. Primary graft nonfunction, leading to graft loss and retransplantation, as well as delayed graft function (DGF) with the need for posttransplant dialysis are the most frequent clinical manifestations of this pathology [5].

Dynamic organ preservation approaches, such as machine perfusion, hold promise for improving organ preservation and resuscitation of marginal donor allografts [6-9]. Although tissue oxygen consumption is markedly decreased at 4-10°C, there is still relevant metabolism at this temperature. Oxygen during machine perfusion is the key ingredient in the protective responses of hypothermic oxygenated machine perfusion (HOPE), with organ reconditioning effectively increasing the cellular energy balance via various mitochondrial pathways [10]. Over time, the addition of oxygen during machine perfusion emerged as a powerful novel tool in organ preservation [11,12]. HOPE is an easy to implement, short-term, end-ischemic reconditioning concept, as the organ perfusion is performed in the transplant center shortly before the actual implantation [11,13]. Ischemia-reperfusion injury occurs upon revascularization of the kidney allograft. Decrease of oxidative metabolism and depletion of adenosine triphosphate (ATP) are the results of the lack of oxygen during ischemia. Reintroduction of oxygen to the ischemic allograft results in massive reactive oxygen species production and release, leading to cellular damage. The mechanisms behind IRI are multifactorial, and ways to minimize its detrimental effects are still the subject of intense debate [14].

In the preclinical setting, the positive effects of HOPE have recently been demonstrated through a reduction in the incidence of tubular damage, macrophage activation, and functional optimization of cellular energy-status in vitro and in vivo [8,9,11]. There are several hypotheses regarding the underlying mechanisms of HOPE-induced organ protection. According to these hypotheses, HOPE presumably exerts its positive effects by: (1) modulating cellular metabolism (energy balance, mitochondrial respiration, IRI); (2) stimulating the vascular endothelial layer; and (3) triggering various subcellular protective pathways (Figure 1) [15]. Investigating the effects of HOPE in a rat model, Kron et al recently demonstrated its beneficial effects on the immune response. Less cytokine release and less T-cell and macrophage activation were measured in the animals receiving the HOPE-treated kidneys [16]. Accordingly, decreased immune response may be one of the key underlying mechanisms of HOPE.

The aim of this prospective cohort study is to investigate the effects of HOPE on ECD kidney allografts donated after brain death. This study utilizes a comprehensive sample collection protocol to assess the subcellular mechanisms of HOPE in the clinical setting.

**Figure 1 figure1:**
[figure not shown]
Hypothermic oxygenated machine perfusion. The donor organ is explanted and transported to the transplant center stored in a box of ice. In the transplant center, the kidney is connected to the Kidney Transport Assist device and HOPE is performed. It is assumed HOPE leads to less oxidative stress, decreased cell death and enhanced energy reserves. Adapted from Czigany et al [<xref ref-type="bibr" rid="ref12">12</xref>]. ET: Eurotransplant, HOPE: hypothermic oxygenated machine perfusion; ATP: adenosine triphosphate; ROS: reactive oxygen species.

## Methods

### Study Type and Eligibility

The present trial is an investigator-initiated pilot study on the effects of HOPE on ECD-allografts in donated after brain death kidney transplants. Figure 2 summarizes the trial design.

Patients older than 18 years of age, suffering from end-stage renal disease (ESRD), listed for kidney transplant, and receiving ECD organs at the Department of Surgery and Transplantation, University Hospital Rheinisch-Westfälische Technische Hochschule (RWTH) Aachen, Aachen, Germany, are eligible for the study. Informed consent was obtained from all subjects participating in the trial by a qualified member of the study team. Inclusion and exclusion criteria are listed in Textbox 1.

**Figure 2 figure2:**
[figure not shown]
Study flow chart. ECD: extended criteria donor; HOPE: hypothermic oxygenated machine perfusion; DGF: delayed graft function; GFR: glomerular filtration rate.

Study inclusion and exclusion criteria.
*Inclusion Criteria:*
Signed informed consent18 years or olderSuffering from ESRD (end-stage renal disease)Listed for kidney transplantReceiving ECD (extended criteria donor)-allografts
*Exclusion criteria:*
Recipients of living donor kidney transplantsPrevious solid organ transplantationCombined procedures (eg, kidney-liver transplantation)Participation in other kidney-related trialsThe subject received an investigational drug within 30 days prior to inclusionThe subject is unwilling or unable to follow the procedures outlined in the protocolThe subject is mentally or legally incapacitatedNon-German or non-English speakersFamily members of the investigators or employees of the participating departmentThe subject suffers from uncontrolled bacterial or viral infection

### Organ Procurement and Definition of Extended Criteria Donor Criteria

ECD kidney allografts will be retrieved by local procurement teams with the Eurotransplant network. Following cross-clamping (*in situ* flushing of the abdominal organs and the beginning of cold ischemia time), allografts will be removed and transported in a standardized fashion on packed ice. Required data regarding the donor and the organ will be collected and will be transferred to designated case report files (CRFs).

As per previous studies [4,17] deceased donors must be ≥60 years old, but it is possible for those aged between 50-59 years old to be donors if they have at least two of the following conditions: (1) cerebrovascular cause of death; (2) serum creatinine greater than 1.5 mg/dL (132.6 µmol/L); or (3) history of arterial hypertension.

### Hypothermic Oxygenated Machine Perfusion Versus Historic Cold Storage Group

Primary and secondary outcomes of patients transplanted with the HOPE-treated kidneys will be compared to a case-matched group of 30 patients (1:2 matching) transplanted with ECD organs after conventional cold storage, using identical surgical techniques and perioperative treatment at the Department of Surgery and Transplantation, University Hospital RWTH Aachen. The present trial comprises two groups, a perfusion (Group 1, HOPE) and a control conventional cold storage group (Group 2, Historic). Patients on the waiting list for kidney transplant with proven written consent will be recruited. HOPE will be applied to the allograft in the operating room after regular organ procurement, transport, and back-table preparation (Figure 1).

We adapted a protocol based on clinical studies with nonoxygenated hypothermic machine perfusion, and on preclinical experience with HOPE [11,18,19]. HOPE will be applied through the renal artery for at least two hours, with a perfusion pressure of 25 mmHg and a perfusion rate of 50-200ml/min using 1 L of recirculated perfusate at 0-4°C. The perfusate will be oxygenated using medical grade oxygen (O^2^), with a partial pressure of oxygen (pO^2^) of 60-80 kilopascals (kPa), by an oxygenator included as a disposable part of the setup. Perfusion parameters registered by the device will be stored automatically and evaluated for possible patterns. Immediately prior to perfusion, grafts will be flushed with perfusate solution to wash out the residual histidine-tryptophan-ketoglutarate (HTK) solution. Storage, management, and use of the medical products will be carried out according to the manufacturer’s guidelines.

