### Sample Collection and Storage

Ischemia reperfusion injury will be assessed using kidney tissue samples taken upon arrival of the organ (before HOPE) and at the end of implantation after reperfusion, but before closure of the abdomen, to evaluate the extent of IRI (Figure 3). In total, two biopsies using BARD MONOPTY Disposable Core Biopsy Instrument (Bard Biopsy Systems Inc, Tempe, Arizona) will be harvested from the ECD kidney allograft and used for translational research. During machine perfusion, perfusate samples will be collected every 20 minutes. Blood samples are taken as part of the daily routine during the perioperative and postoperative course of kidney transplant (Figure 3). Blood parameters of kidney function (ie, creatinine, urea, estimated glomerular filtration rate [eGFR]) will be monitored. An additional 20 mL of blood will be drawn on postoperative days 1, 2, 3 and 7 and will be used for translational research (Figure 3). All kidney tissue, serum, and perfusate will be directly snap-frozen in liquid nitrogen (−80°C) and stored for 6 months after completion of the trial. To assess the subcellular mechanisms of HOPE in the clinical setting, various parameters, including markers of kidney injury (creatinine and neutrophil gelatinase-associated lipocalin (NGAL) in plasma samples), tissue ATP concentration, inflammatory mediators (eg, tumor necrosis factor alpha, interleukin-6, macrophage migration inhibitory factor, interleukin-10, monocyte chemoattractant protein-1), and biomarkers of oxidative damage (eg, 8-hydroxy-2'-deoxyguanosine), will be analyzed [11,12].

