### Study Endpoints

The primary endpoint is DGF, which is defined as the need for dialysis in the first 7-days posttransplantation. The secondary endpoints of the study include: (1) duration of DGF (defined as the period between kidney transplant and last dialysis in days) and functional DGF (defined as <10% fall in serum creatinine for 3 consecutive days in the first week posttransplantation); (2) creatinine reduction ratio day 2 ([creatinine day 1−creatinine day 2]/creatinine day 1) and Creatinine reduction ratio day 5 ([pretransplant creatinine−creatinine day 5]/pretransplant creatinine); (3) incidence of postoperative complications, as assessed by the Clavien-Dindo complication score and the comprehensive complication index [22]; (4) duration of intensive care and hospital stay; (5) recipient and graft survival after six months; (6) renal function (assessed by serum creatinine and eGFR) at one-, three- and six-months post-transplant; and (7) basic and translational research, which involves assessing biomarkers from routinely harvested kidney tissue and serum following implantation to obtain information on kidney injury, extent of oxidative damage, redox- and energetic homeostasis of the implanted donor kidney.

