### Study Population

To the best of our knowledge, aside from a sole case of HOPE-treated dual kidney transplant reported recently, no experience of HOPE in human donation after brain death kidney transplant has been published yet [23]. In the present pilot study, 15 patients (N=15) will be treated with HOPE to gain first prospective clinical knowledge. HOPE-treated patients will be compared to a case matched group of 30 patients (N=30).

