### Ischemia-Reperfusion Injury and Inflammation

IRI is an inevitable event in organ transplantation. Reduction of oxygen delivery because of blood flow interruption leads to anaerobic metabolism and the production of oxygen-free radicals and oxidative stress as a respiratory burst at the onset of reperfusion. IRI plays a key role in DGF and primary graft nonfunction following kidney transplantation, depending on initial organ quality [8,9,24,25]. To detect the effects of HOPE on IRI, the kidney tissue, blood, and perfusate samples obtained in this study will be used to quantify several innovative parameters of inflammation (eg, interleukins, tumor necrosis factor-alpha), kidney injury (Cytatin-C, NGAL, etc) energy- (ATP levels) [11,26], and redox-threshold (Hemoxygenase-1, Malondialdehyde) [12,27]. Luminometry, Spectrophotometry, Luminex-assay, Enzyme-linked immunosorbent assay (ELISA), Reverse transcriptase polymerase chain reaction (RT-PCR) and Western blot will be used for these analyses. Proteomics and metabolomics analysis will be performed on kidney tissue samples to potentially identify early mediators of HOPE-mediated organ protection.

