We identified four active clinical trials exploring the effects of HOPE in kidney transplantation. In a pilot study by Ravaoili et al, 20 subjects were recruited to receive either HOPE-treated ECD-kidney or ECD-liver allografts. Whether the organs used were donated after cardiac death or donated after brain death remains unclear (NCT03031067; Table 1). One trial (NCT02621281) is a large multi-center RCT investigating HOPE in donated after cardiac death kidney transplantation, including ECD and nonECD allografts in a large Chinese cohort. Two relevant trials of the Consortium for Organ Preservation in Europe are recruiting in a large collective of patients. The Cold oxygenated machine preservation of aged renal donation after cardiovascular death transplants (COMPARE) trial (ISRCTN32967929), initiated at the University Hospital Leuven, Belgium, included a total of 102 transplanted donated after cardiac death kidney pairs that are being used to discover whether continuous oxygenated machine perfusion is superior to nonoxygenated machine perfusion. The COMPARE trial has a considerably different design compared to our study, with a logistically complex perfusion concept involving the transport of the machines to the retrieval center and applying continuous HOPE. Preimplantation oxygenated hypothermic machine perfusion reconditioning after cold storage (COPE-POMP) (ISRCTN63852508), initiated from the University Hospital of Essen, Germany, is currently ongoing and involves randomizing ECD allografts to end-ischemic preimplantation HOPE or to conventional cold storage.

Although we have designed our trial carefully, nonrandomization of the study groups and nonblinding of the transplant team, as well as matching with a historical group, are limitations of the present study. Nevertheless, conclusive clinical data about end-ischemic HOPE in human kidney transplantation are still missing and larger multi-center studies on this topic are currently underway. Therefore, it seems plausible to conduct this trial as a pilot study with a focus on short-term outcomes as well as translational research aspects of HOPE in ECD-kidney transplantation.

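### The article promises a comparison with historic controls for all secondary outcomes, but describes no control samples for the biomarker endpoint, so its results cannot be attributed to HOPE as planned

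*Protocol article*

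**What the plan says.** The section on HOPE versus the historic cold storage group sets the comparison: "Primary and secondary outcomes of patients transplanted with the HOPE-treated kidneys will be compared to a case-matched group of 30 patients (1:2 matching"). It describes the comparator as "a control conventional cold storage group (Group 2, Historic"). Study Population gives the treated group: "15 patients (N=15) will be treated with HOPE to gain first prospective clinical knowledge".

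Study Endpoints numbers seven secondary endpoints. The seventh is "basic and translational research, which involves assessing biomarkers from routinely harvested kidney tissue and serum following implantation".

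Sample Collection and Storage sets out the material:
- Tissue: "kidney tissue samples taken upon arrival of the organ (before HOPE) and at the end of implantation after reperfusion".
- Blood: routine daily samples for creatinine, urea and eGFR, and beyond these, "An additional 20 mL of blood will be drawn on postoperative days 1, 2, 3 and 7 and will be used for translational research".
- Perfusate: every 20 minutes while the machine runs.

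The section on ischemia-reperfusion injury and inflammation gives these samples their purpose: "To detect the effects of HOPE on IRI, the kidney tissue, blood, and perfusate samples obtained in this study will be used". It also hopes that proteomics and metabolomics will point to early mediators of protection by HOPE. The Introduction names the study of subcellular mechanisms as what the sample collection is for. The Discussion counts it as a strength that the same staff collect samples under study protocols throughout the study period.

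**The concern.** A statement that a biomarker changed because of HOPE needs either comparable samples from kidneys that did not receive HOPE, or a within-graft contrast in which HOPE is the only thing that happened between two samples. The article promises the first for every secondary outcome but describes sampling only for prospectively treated patients. The second is not available from the biopsies, because none is taken between the end of HOPE and reperfusion.

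What is at stake is the mechanistic part of the trial. If the plan is followed as written, a before/after change in 15 uncontrolled grafts could be reported as an effect of HOPE on ischemia-reperfusion injury when implantation and reperfusion contributed to it to an unknown degree.

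**Working it through.** No formula applies. The article gives no power calculation or other derived figure for this endpoint. The one piece of arithmetic, the 1:2 matching, is consistent: 15 × 2 = 30. The check is to set the sections side by side.

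**Step 1: does the promised comparison include the biomarkers?** The comparison covers secondary outcomes without exception, and Study Endpoints lists the biomarker work as secondary endpoint (7). Read literally, it is included.

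**Step 2: what control material does the article describe?**

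| Material | HOPE group | Historic cold storage group |
|---|---|---|
| Biopsies on arrival and after reperfusion | Planned, for translational research | None described |
| Research blood, days 1, 2, 3 and 7 | Planned, additional to routine | None described |
| Perfusate | Every 20 minutes during perfusion | Cannot exist: grafts were not perfused |
| Routine creatinine, urea, eGFR | Planned | Plausibly available from routine care |

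The section on ischemia-reperfusion injury limits the material to samples obtained in this study, and the Discussion describes prospective collection. Neither points to an archive of control samples.

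**Step 3: can a within-graft contrast take the place of a control?**
- Biopsies. The first precedes HOPE and the second follows reperfusion. The change between them is the sum of whatever HOPE, implantation and reperfusion each did, and one difference cannot be split into three parts. The article itself describes reperfusion as a source of reactive oxygen species and oxidative stress, which are among the pathways that endpoint (7) measures.
- Research blood. Every draw is postoperative, so there is no value from before HOPE.
- Perfusate. These samples come before reperfusion, so reperfusion cannot explain a trend in them. But nothing shows what would have happened without oxygenation or without perfusion. They describe the course during HOPE, not its effect.

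**Step 4: does the planned analysis supply a control?** Data Collection and Statistics specifies a two-way analysis of variance for laboratory time courses without naming the factors. If one factor is treatment group, values are needed in both groups at the same times. From what is described, only the routine parameters can be expected to meet that.

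**The case against.** The strongest case on the other side has four parts.

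1. *Silence is not absence.* A reader might infer that the historic controls have no tissue or blood at all, that is, 15 patients against none on every marker. The documents do not support this. Only the lack of perfusate is certain. Study Endpoints calls the tissue and serum routinely harvested, which leaves archived material possible. The article condenses a fuller protocol, and the flow chart and visit figure are not shown. This part stands, and the point is worded accordingly. It does not remove the point: the research blood is expressly additional to routine, the biopsies are for translational research, and no archive is mentioned.

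2. *The comparison may be meant for clinical outcomes only.* The abstract lists only clinical secondary endpoints and describes the sampling in a separate sentence. That is a reasonable guess at the intention, but the Methods text does not say it, and the numbering in Study Endpoints contradicts it. If it is the intention, the fix simply writes it down.

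3. *Not everything is confounded with reperfusion.* A reader might infer that reperfusion alone could explain every change. For perfusate that is wrong, since it is sampled before reperfusion. It remains uncontrolled.

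4. *The aims are exploratory and the limits are conceded.* This is a pilot, the mechanistic hopes are hedged, and the Discussion admits that nonrandomization, nonblinding and "matching with a historical group, are limitations of the present study". This lowers the weight of the point. But conceding that a comparison may be biased is different from disclosing that, for one endpoint, the described data contain no comparison.

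**Conclusion.** The point holds in a limited form. The article promises a between-group comparison for secondary endpoint (7) and identifies no control samples with which to make it. The paired biopsies in the 15 HOPE grafts cannot separate HOPE from implantation and reperfusion, and the perfusate series has no control. As described, endpoint (7) supports description within the HOPE group, not attribution to HOPE.

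This rests on two assumptions: that the article's account of sampling is complete as to which group is sampled, and that no archived samples from cold-storage recipients of extended criteria kidneys are to be used. If such samples exist, the point shrinks to naming them and restricting the comparison to what matches.

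A reader might go further and conclude that the trial's main results are compromised. Nothing here supports that: delayed graft function, the clinical endpoints and safety do not depend on these samples. The text should be corrected because the change alters what the trial may conclude about mechanism, but the fault is not a critical one.

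**What to change.** - In the section on HOPE versus the historic group, exclude endpoint (7) from the comparison with the 30 matched patients.
- In Study Endpoints, label endpoint (7) descriptive and exploratory within the HOPE group: time course of markers, and association of markers with delayed graft function among the 15. Reconcile the description of the samples as routinely harvested with the study-specific sampling in Sample Collection and Storage.
- Limit between-group laboratory comparisons to routine parameters recorded in both groups (creatinine, urea, eGFR).
- Align the Introduction, Sample Collection and Storage, the section on ischemia-reperfusion injury and the Discussion, so that effects of HOPE on that injury, or protection mediated by HOPE, are not offered as conclusions these data can support.
- State whether archived samples from cold-storage recipients of extended criteria kidneys exist. If they do, name them and compare only the matching markers and time points.

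The cost is a weaker mechanistic claim. No new samples or procedures are needed, and clinical management does not change.
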